### Randomization and blinding

2.5.

This study applies a randomized stratified block design. According to the number of research centres, it is divided into four strata. In each stratum, the number of blocks is 2, and the length of the blocks is 4. The eligible children will be randomly assigned to Group A and Group C at a ratio of 1:1. The randomization will be completed by SAS software (SAS Institute Inc., USA). The allocation information will be concealed in sealed, opaque envelopes and opened by the anaesthesiologists in charge before the children enter the preoperative waiting room. To ensure the participants' safety and to complete warming measures, the anaesthesiologists in charge will not be blinded, and they will not participate in follow-up or results analysis. In addition, the allocation information will be blinded for patients and the researchers in charge of follow-up. The interim analysis will be completed by researchers independent of the overall trial process.

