### Intervention

2.4.

A total of 400 children will be randomly assigned to the active warming strategies group and the control group. The specific warming measures are as follows.

**Active warming strategies group (Group A):** Details about the active warming strategy are mainly described in Figure 3, which was carried out in a total of three locations, including the preoperative waiting room, the operating room and the postanaesthesia care unit (PACU). In the preoperative waiting room, pre-warming is mainly carried out using a forced-air warming blanket (40°C). If the child's body temperature is <36°C or subjectively feels cold, we further raise the temperature of the forced-air warming blanket and the temperature of the waiting room. Active warming measures in the operating room are to maintain the forced-air warming blanket at 40°C, the infusion equipment at 37°C, the body cavity lavage liquid at 38°C and the operating room temperature at 24°C. Active warming measures in the PACU are to maintain the forced-air warming blanket at 40°C, the infusion equipment at 37°C and the room temperature at 24°C. Real-time temperature monitoring will be maintained throughout the whole process. The nasopharyngeal core temperature will be monitored additionally for correction after anaesthesia induction and before awakening. All active warming measures will be discontinued on exit from the PACU.

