**Figure 3 F3:**
[figure not shown]
Active warming strategies process.

**Control group (Group C):** Routine passive warming measures will be used in the perioperative period. Children will be covered in insulation layers from entering the preoperative waiting room to leaving the PACU. In the preoperative waiting room, the children will still use a warming blanket but not heated forced air and not raise the room temperature. In the operating room, the warming blanket is not heated and the rest of the warming measures, including the infusion equipment, the body cavity lavage liquid, and the temperature of the operating room, is at the discretion of the anaesthesiologist in charge. In the PACU, the warming blanket is also not heated and the rest of the warming measures, including the infusion equipment, and the temperature of the operating room, is at the discretion of the anaesthesiologist in charge. Similarly, real-time temperature monitoring will be maintained throughout the whole process. The nasopharyngeal core temperature will be monitored additionally for correction after anaesthesia induction and before awakening. If the children's temperature is <35°C throughout the perioperative period, regulations for body temperature protection will be enforced as described below.

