#### Secondary outcomes

2.7.2.

(1)Cumulative hypothermia effect value (*Σ Δ*T_i_ × *Δ*t_i_, i = 1…, *n*) in the preoperative waiting room, operating room, and PACU;(2)Difference value between intraoperative core temperature and axillary temperature;(3)Results of arterial blood gas analysis in the anaesthesia recovery period, including pH, lactic acid, and haemoglobin values;(4)Shivering score, Cornell Assessment of Pediatric Delirium score, and thermal comfort score in the anaesthesia recovery period;(5)Body temperature in the morning of the first day after surgery;(6)The incidence of incision infection during hospitalization;(7)The morbidity of major complications during postoperative hospitalization;(8)Length of stay and expenses;(9)All-cause mortality 30 days after the operation.

Note: a. Anaesthesia recovery period refers to the time from stopping anaesthetic infusion to the time when the children are completely conscious and fully awake. b. Major complications during postoperative hospitalization include postoperative pulmonary complications, arrhythmias requiring treatment, myocardial infarction, sepsis, renal failure, central nervous system events, anastomotic leakage, and accidental transfer to the intensive care unit.

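### The protocol says patients are blinded to allocation, but awake children can feel whether their blanket is heated, so thermal comfort, where self-reported, is not a blinded outcome

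*Protocol article*

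**What the plan says.** Section 2.5 (Randomization and blinding) sorts the people in the trial into two groups. On one side, "the anaesthesiologists in charge will not be blinded, and they will not participate in follow-up or results analysis". On the other, "the allocation information will be blinded for patients and the researchers in charge of follow-up".

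Section 2.4 (Intervention) describes what each child receives. Group A is pre-warmed in the waiting room under a forced-air blanket at 40°C. The child's own sensation feeds back into the setting: "If the child's body temperature is <36°C or subjectively feels cold, we further raise the temperature of the forced-air warming blanket", and the waiting-room temperature is raised as well. The body temperature protection rules in the same section add that, in Group A, the blanket is turned down if the child complains of heat. After surgery, "Active warming measures in the PACU are to maintain the forced-air warming blanket at 40°C".

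In Group C, in the waiting room, "the children will still use a warming blanket but not heated forced air and not raise the room temperature". Later, "In the PACU, the warming blanket is also not heated".

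Section 2.7.2 lists, as item (4) of nine secondary outcomes, "Shivering score, Cornell Assessment of Pediatric Delirium score, and thermal comfort score in the anaesthesia recovery period". Its note defines that period as running from the stop of the anaesthetic infusion until the child is fully awake.

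**The concern.** Blinding of patients is stated as a feature of the design, so a reader will judge the risk of bias with it in mind. Here the treatment contrast is heat on the skin, delivered while the child is conscious. If the child can tell the arm, the statement is wrong as it stands, and any outcome that depends on the child's report lacks the protection it appears to have.

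Thermal comfort is the outcome most at stake, because it asks about the same sensation that reveals the arm. The Abstract and the Discussion use the secondary outcomes together to assess prognosis. What the comfort result can support therefore depends on whether it is understood to be unblinded.

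**Working it through.** No arithmetic applies, because the blinding statement involves no figure. The check sets the statement in section 2.5 against what the other sections say happens to the child.

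1. **Can the child perceive the treatment before induction?** Both arms have a blanket in the waiting room. In Group A it blows air at 40°C; in Group C the air is not heated and the room is not warmed (section 2.4). The arms differ in something that is felt directly. Section 2.6 gives midazolam before induction, within the operating-room sequence, so nothing there shows that it masks the earlier waiting-room period.

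2. **Does the treatment respond to the child?** In Group A, feeling cold leads to more heat and complaining of heat leads to less (section 2.4). Group C has no matching adjustment to sensation; its only trigger for forced warming is a temperature below 35°C.

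3. **Does the child have the information to interpret the sensation?** Section 2.2 says that children and their guardians are told about the protocol between admission and the day before surgery, and that school-age children sign consent. An older child, or a guardian, who knows the comparison can read the arm from heated air or its absence. This is weaker for toddlers, but eligibility runs from 1 to 12 years (section 2.3.1).

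4. **Does the contrast persist while the recovery scores are taken?** The recovery period begins when the infusion stops at the end of surgery, and transfer to the PACU comes after extubation (sections 2.6 and 2.7.2). Scoring may therefore fall in the operating room or the PACU. In both places the Group A blanket is set to 40°C and the Group C blanket is not heated. Group A warming ends only on leaving the PACU (section 2.4).

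5. **Does the assessor blinding cover the recovery scores?** It applies to the researchers in charge of follow-up. Section 2.7.3 places follow-up in the postoperative hospital stay and at day 30, and lists PACU data under a separate entry. The blinding therefore does not clearly reach the recovery period.

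6. **Which outcomes are touched?**
   - Primary outcome: temperature below 36°C accumulated over time (section 2.7.1). It is an instrument reading and is little affected.
   - Thermal comfort: exposed to the extent that the child is the respondent.
   - Shivering and delirium: if they are rated by an observer, blinding depends on whether that observer can see or feel the device. The article does not name the rater.

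**The case against.** The strongest reply has four parts.

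- **Feeling warm is not the same as knowing the allocation.** Section 2.5 speaks of allocation information, both arms have a blanket, and a one-year-old will draw no conclusion. Equipment is also not a perfect marker of the arm: other warming in Group C is at the anaesthesiologist's discretion, active warming starts in either arm below 35°C, and a Group A blanket may be turned down. This stands for the youngest children and for some individual cases. It does not rescue a general statement that patients are blinded, given that families have been told the protocol and heated air is the routine difference between the arms.

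- **The article never says that the recovery scores are blinded.** A reader might infer that all three scores are open-label outcomes presented as blinded. The documents do not support that. Section 2.7.2 makes no blinding claim, no rater is named, and nothing says that thermal comfort is self-reported. For shivering and delirium, an open-label rating is a possibility and not a stated fact. Rater details may also stand in a fuller protocol.

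- **The direction of bias is not given.** A reader might infer that comfort scores must be biased in favour of Group A. Greater comfort under a heated blanket may simply be the treatment effect, and section 2.4 itself foresees Group A children who complain of heat. No direction or size should be asserted.

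- **The primary outcome is not a subjective score.** This stands, and it limits the weight of the point.

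**Conclusion.** The point holds in a limited form. The claim that patients are blinded is contradicted by the interventions described in section 2.4, and it should not stay in the protocol.

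The consequence falls chiefly on thermal comfort, one of the three scores in one of nine secondary outcome items. This rests on the assumption that at least the older children report comfort themselves. Shivering and delirium scores join it only if their rater is not masked to the device. The effect on the primary outcome is small, and the size of any bias in the comfort score cannot be derived from the documents.

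The correction is worth making because it is specific and cheap, and because it changes how the comfort result may be interpreted.

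**What to change.** In section 2.5, remove the claim that patients are blinded. State that patients and the anaesthesiologist in charge are not blinded, and limit the blinding claim to the assessors who carry out follow-up during the hospital stay and at day 30.

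Treat and report thermal comfort as an unblinded outcome. Do the same for the shivering and delirium scores unless they are rated by someone masked to the warming device. It would help to say who rates each of the three scores and whether that person can see or feel the device.

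The cost is a less favourable blinding statement. The intervention, the sample size and the primary analysis are unchanged. If a masked rater is introduced for shivering and delirium, that adds a staffing demand; reporting those scores as unblinded avoids it.

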#### Other data to be recorded

2.7.3.

**Preoperative:** Baseline data, including demographic characteristics, basic vital signs, complications, and information related to anaesthesia and operation.

**Intraoperative:** Record vital signs and respiratory parameters every 10 min during anaesthesia, the type and dose of intraoperative medicines, intraoperative adverse events, total fluid volumes, and the durations of anaesthesia, surgery, and the recovery period.

**Postoperative:** The PACU stay period, medicine administration, Ramsay Sedation score and Wong-Baker Faces Scale scores recorded when the patient leaves the PACU.

**Follow-up:** Will be conducted during postoperative hospitalization and on the 30th day after the operation.

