### Sample size calculation

2.8.

This study is a multicentre, prospective, randomized controlled trial. According to the pretest, the mean ± standard deviation of the perioperative cumulative hypothermia effect value (*Σ Δ*T_i_ × *Δ*t_i_, i = 1…, *n*) under passive warming measures is 12.2 ± 4.31, and using perioperative active warming strategies, it can be decreased by 15%. Considering a dropout rate of 20%, 400 subjects will be required with 90% power and an *α* level of 0.05. The sample ratios of the four centres are *Q*_1 _= *Q*_2 _= *Q*_3_= *Q*_4 _= 1/4N = 100.

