### Statistical analysis

2.11.

Statistical analysis will be performed by SPSS software, version 24. (International Business Machines Inc., USA). Continuous variables will be reported as the mean ± standard deviation ($\bar{x}\pm s$) or medians and interquartile ranges. Categorical variables will be presented as numbers (proportion, %). The Kolmogorov-Smirnov test will be performed to detect the normal distribution of continuous variables. Student's t test will be used for normally distributed continuous variables, and the Kruskal-Wallis H test will be used for abnormally distributed data. The grade variables will be analysed using the Mann-Whitney U test. The chi-square test and Fisher's exact test will be used to analyse categorical variables. Repeated measures analysis of variance will be applied for the analysis of repeated measures data. *p* < 0.003 is defined as statistically significant in interim analysis, and the statistical significance of the final analysis is set at *p* < 0.05.

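### The blinding stated in section 2.5 does not reach the primary outcome: its readings are complete at PACU exit, before the blinded follow-up staff begin, and the only staff role named in those rooms is unblinded

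*Protocol article*

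**What the plan says.** Section 2.5 leaves the anaesthesiologists in charge unblinded, for safety and so that they can deliver the warming, and adds that "they will not participate in follow-up or results analysis". It then states that "the allocation information will be blinded for patients and the researchers in charge of follow-up". Section 2.7.3 says of follow-up: "Will be conducted during postoperative hospitalization and on the 30th day after the operation".

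The primary outcome (2.7.1) sums the shortfall below 36°C multiplied by its duration. Secondary outcome (1) splits the same quantity by waiting room, operating room and PACU. Secondary outcome (2) is the intraoperative difference between core and axillary temperature.

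On measurement, section 2.4 says of Group A: "Real-time temperature monitoring will be maintained throughout the whole process", and says the same in substance of Group C. In both groups a nasopharyngeal reading is added after induction and before awakening, to correct the axillary signal. Section 2.7.3, under other data, has the instruction "Record vital signs and respiratory parameters every 10 min during anaesthesia".

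Section 2.9 says that at the interim analysis researchers not directly involved in it stay blinded. It names no role.

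**The concern.** The blinding rule is written around follow-up, but the primary outcome is not a follow-up measurement. It is built up in three rooms where the one named staff role knows the allocation, having opened the envelope. That role is excluded from later outcome assessment and from analysis, but not from taking, noting or correcting temperatures.

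The outcome is a sum of small departures from a fixed threshold, so a small difference between arms in how readings are taken or corrected would pass straight into the treatment comparison. A systematic lean of this kind does not shrink as more children are enrolled. If values were charted by hand and no trace kept, it could not be undone later.

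**Working it through.** **Step 1: who is blinded, and when the outcome is complete.**
- Named as blinded: patients and follow-up researchers (2.5).
- Named as unblinded: the anaesthesiologists in charge (2.5), barred from follow-up and results analysis.
- Primary outcome and secondary outcome (1): waiting room, operating room and PACU (2.7.2). Secondary outcome (2): intraoperative.
- Follow-up: postoperative hospitalization and day 30 (2.7.3).

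That the primary outcome ends at PACU exit is an inference, but a well-supported one. Secondary outcome (1) names those three rooms, the warming measures stop on leaving the PACU (2.4), and the next-morning temperature is a separate outcome, (5). No staff role named as blinded is therefore placed where the primary readings arise.

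**Step 2: the plan's target difference.** Section 2.8 says that the pretest value "under passive warming measures is 12.2 ± 4.31, and using perioperative active warming strategies, it can be decreased by 15" per cent. Target = 0.15 × 12.2 = 1.83.

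The stated total of 400 does not follow from these inputs. With two-sided α 0.05 and 90% power, n = 2 × (1.960 + 1.282)² × 4.31² / 1.83² gives 117 per arm. Then 117/0.8 rounds up to 147 per arm, or 294 in total. That is a separate matter and does not affect the 1.83 used here.

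**Step 3: the unit.** None is stated. °C·min is assumed. Under °C·h, with depth roughly limited to 1°C because both groups are actively warmed below 35°C (2.4), a value of 12.2 would need about 12 hours or more below 36°C, which is implausible.

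**Step 4: how large a one-arm lean would have to be.** Approximate shift in the arm mean = lean × minutes below 36°C. Minutes needed to equal the target:
- 1.83 / 0.1 = 18.3 min
- 1.83 / 0.05 = 36.6 min

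The same formula at other durations, with the mean depth that would give 12.2 (depth = 12.2 / minutes):

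| Minutes below 36°C | Mean depth, °C | Shift at 0.05°C (share of 1.83) | Shift at 0.1°C (share of 1.83) |
|---|---|---|---|
| 20 | 0.61 | 1.00 (55%) | 2.00 (109%) |
| 24.4 | 0.50 | 1.22 (67%) | 2.44 (133%) |
| 36.6 | 0.33 | 1.83 (100%) | 3.66 (200%) |
| 60 | 0.20 | 3.00 (164%) | 6.00 (328%) |

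The durations, depths and leans are assumptions; the article gives none of them. If the unit were °C·h after all, the two break-even times would be 18.3 and 36.6 hours.

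**The case against.** **The monitor may log automatically.** The article describes a real-time axillary sensor and nowhere says that a person reads or writes the primary-outcome values. Automatic logging would largely close the charting route. This stands, and it is why the point is an exposure. The correction step would still be open to the unblinded role.

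**The 10-minute rule.** A reader might infer that this rule shows hand entry of the primary outcome. It does not. It sits under other data to be recorded and covers vital signs and respiratory parameters during anaesthesia, whereas the primary outcome also spans the waiting room and the PACU.

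**False-positive rates.** A reader might also turn a lean into an inflated error rate. With 160 evaluable per arm (400 less 20%), SE = 4.31 × √(2/160) = 0.482, and the significance threshold is 1.96 × 0.482 = 0.94. A lean of 0.05°C over 24.4 to 61 minutes would shift the mean by 1.22 to 3.05 and give false-positive rates of 72% to nearly 100%. The arithmetic is right, but any assumed one-arm bias of that size produces such rates. The unit, depth and lean are not in the article, so the figures say nothing about how likely a bias is. With readings in 0.1°C steps, a mean lean of 0.05°C would need half of one arm's readings below 36°C to be off by a full step in the same direction. Nor does the outcome jump at the threshold: a reading of 35.9°C adds only 0.1 × its duration.

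**Existing safeguards.** The anaesthesiologists are barred from results analysis, where the sum may well be derived, and section 2.9 keeps other researchers blinded. Both help downstream. Neither supplies a blinded role for taking or correcting the readings.

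**Condensation.** An article may leave data capture to the full protocol. That is fair for device details. But section 2.5 does state a blinding rule, and the rule as stated stops short of the primary outcome.

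**Conclusion.** The point holds as a gap in the stated blinding, not as a demonstrated error. The named blinded staff begin work after the primary outcome and secondary outcomes (1) and (2) are complete, and nothing stated keeps the unblinded role away from the readings or their correction.

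The article does not support the stronger conclusions that temperatures are charted by hand, that a lean will occur, or that 0.05°C is in general enough to match the target. It matches 1.83 only at about 37 minutes below 36°C, and 0.1°C matches it at about 18 minutes, both on the assumption of °C·min. Confidence is moderate: the timing rests on reading several sections together, and the practical size of the exposure depends on how readings are logged, which is not stated. The change is worth making because it is cheap and alters no treatment.

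**What to change.** State in sections 2.5 and 2.7.1 that the primary outcome and secondary outcomes (1) and (2) are computed from the time-stamped trace of the real-time monitor, exported under the child's code. Prespecify one core-temperature correction rule, identical in both arms, and have it applied by someone without the allocation. Where a centre's device cannot export, fix the reading times in advance and record the displayed value unrounded.

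The cost is protocol wording, export set-up at four centres and a fallback for devices that do not store data. That the monitors do store data is an assumption to check at each centre. The change does not remove differences between arms in how the probe is placed or handled.

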### Standardized anaesthesia management

2.6.

All eligible children will receive standardized anaesthesia management procedures. Except for real-time axillary temperature monitoring, when the children enter the operating room, standard monitoring will be applied, including noninvasive blood pressure, heart rate, and pulse oximetry saturation. Invasive arterial pressure, end-tidal carbon dioxide partial pressure, anaesthesia gas monitoring, and the nasopharyngeal core temperature will be monitored after anaesthesia induction. Before anaesthesia induction, the anaesthesiologist in charge intravenously will administer midazolam (0.025–0.075 mg·kg^−1^). General anaesthesia will be induced with sufentanil 0.5 μg·kg^−1^, propofol 2–3 mg·kg^−1^, and cis-atracurium 0.1–0.2 mg·kg^−1^ or rocuronium 0.4–0.6 mg·kg^−1^. After intubation, mechanical ventilation will be set in the volume-controlled mode. The tidal volume will be 8–10 ml·kg^−1^ and the respiratory rate will be 14–20 breaths per minute. Remifentanil (0.1–0.2 μg·kg^−1^·min^−1^) and propofol (8–10 mg·kg^−1^·h^−1^) will be used to maintain the total intravenous infusion anaesthesia and adjusted for sedative and analgesic needs during the operation. Corresponding treatment will be administered according to the children's status to maintain the mean arterial pressure and heart rate within 30% of the baseline values intraoperatively. The infusion of propofol and remifentanil will be stopped at the end of surgery. After extubation, children will be transferred to the PACU and further transferred to the inpatient ward or intensive care unit based on their condition.

